## Abstract

**Introduction:** Fibromyalgia (FM) is characterized by multiple symptoms including pain, fatigue, and sleep disorders, altering patient's quality of life. In the absence of effective pharmacological therapy, the last European guidelines recommend a multidisciplinary management based on exercise and education. Thus, our main objective was to measure the effectiveness of a healthcare organization offering a specific program of adapted physical activity combined with a therapeutic education program for FM patients.

**Methods and Analysis:** The From Intent To Move (FIMOUV) study will recruit 330 FM patients randomized into two groups: test and control. The test group will benefit from a 1-month mixed exercise training program supervised at the hospital, followed by 2 months in a community-based relay in a health-sport structure. In addition, each of the two groups will benefit from therapeutic patient education sessions. The main endpoint is the measurement of the level of physical activity by accelerometry at 1 year. The secondary endpoints concern adherence to the practice of physical activity, impact on lifestyle, state of health, and physical capacity, as well as an estimate of the budgetary impact of this management strategy.

**Discussion:** This interventional research will allow us to assess the evolution of behaviors in physical activity after an FM syndrome management based solely on patient education or based on a supervised and adapted practice of physical activity associated with this same therapeutic education program. It seems to be the first study evaluating the impact of its intervention on objective data for measuring physical activity and sedentary behavior *via* accelerometry among FM patients.

**Trial registration:**
ClinicalTrials.gov NCT04107948.

## Introduction

Fibromyalgia (FM) affects 2–5% of the adult population, with a feminine predominance (1). This syndrome is characterized by multiple symptoms including pain, fatigue, and sleep disorders, altering patient's quality of life (2). Physiopathology is still poorly understood, but a dysfunction of the central nervous system is evoked, involving various mechanisms of pain pathways (3). Diagnosis of FM is based on the American College of Rheumatology criteria (4, 5) and associates a quantitative pain rating scale (Widespread Pain Index) and a rating scale of the severity of symptoms associated with pain (Symptom Severity Scale). According to these last recommendations (4), FM diagnosis is no more an elimination diagnosis but rests on the scores of these two scales, the chronicity of pain (>3 months), the location of pain (>4/5 regions) and does not exclude an association with another pathology (with lesion or organ damage).

Actually, no treatment can cure FM. Pharmacological management often remains on the prescription of analgesics, antidepressants, and/or antiepileptics, but these therapies are not always effective and often cause undesirable effects (6, 7). Nonpharmacological therapies should be advocated as a first-line treatment for patients suffering from FM, such as the practice of a regular physical activity, exercise being “the only ‘strong for' therapy-based recommendation in the [European League Against Rheumatism, EULAR] guidelines” (8).

Exercise has clinical relevance over several parameters such as fatigue, physical function, and quality of life (9). However, it can be applied by several ways of training. The American College of Sport Medicine (ACSM) elaborates the recommendations in terms of physical activity, applying the frequency, intensity, time, type, volume, and progression principle (10). For FM, there are no precise recommendations.

Endurance training is recommended by different medical societies for FM management (8, 11–14) in the range of two to three sessions a week, allowing to respect a rest period and avoid exacerbation of symptoms, at least for a period of 4–6 weeks in order to see a decrease in symptoms (15, 16) and a change in autonomic function (17). A light-intensity aerobic practice (15, 18) does not allow a decrease in symptom intensity, rather indicating a moderate to vigorous intensity physical activity (MVPA) practice. While high-intensity interval training (HIIT) is increasingly used in several pathologies (19–21), it is only minimally studied in FM. Demonstrating improvements in physical capacities (22, 23), HIIT would also be effective for decrease in fatigue (24, 25), pain tolerance (26), and opioid system (27, 28)—three major issues in FM syndrome—without change in pain or disease activity in patients with rheumatic disease (21). Strength training is less documented than aerobic training. Some studies have worked on weight resistance training (two weekly sessions during 16 weeks) with a progressive load from 50 to 80% of the one-repetition maximum, demonstrating a good compliance and an involvement of force correlated to a decrease of 39% in pain perception (29). This decrease in pain was also measured in a resistance program followed for 8 weeks with three sessions a week (30). Recently, Andrade et al. (17) identified a correlation between resistance training and reduction in psychological symptoms such as anxiety and depression. Muscle stretching and relaxation exercises also showed an impact on pain (31), pain perception and tolerance (32), quality of life, depression, and anxiety (33) in FM patients.

At equal time of activity, Sanudo et al. (34) noticed additional health benefits of a combined training program compared to a single modality program. A mixed training program is defined as combining at least two types of exercises among aerobics, resistance and flexibility training, and demonstrated an interest in quality of life (+7%), fatigue (−13%), and physical function (+11%), translating the clinical relevance of mixed exercise training for adults with FM (9).

Despite the absence of accurate recommendations on training modalities, as defined by the ACSM, a personalized and mixed training seems to be the best practice according to the EULAR recommendations (8), and it is also this type of training that is recommended for people suffering from chronic pain (35). In France, there are no professional recommendations of good practice for the management of FM. The health insurance recommends to physicians to give advice for the progressive upturn of physical activity for each person with FM, “according to its means.”

However, European and French recommendations agree to promote patient education to increase “understanding of the complex nature of the interactions between neurobiological processes, behaviors, and symptoms (36).” It showed beneficial impact on pain and pain catastrophizing (37) despite the different educational strategies. Moreover, an education program would be all the more effective if it is combined with an adapted physical activity (APA) program (38, 39).

Then, the problem is to know if simple advice for physical activity is sufficient (as recommended by the French health insurance and commonly performed in consultation) or if an adapted and supervised physical activity (as recommend by the EULAR) would not be more beneficial as a first intention. Thus, in this study, we want to optimize the care pathways of patients suffering from FM by offering a supervised APA program added to therapeutic patient education sessions. This is a prospective, multicenter, controlled, randomized, open-label intervention in two groups. The primary objective of this study is to measure the effectiveness of a healthcare organization offering APA for FM patients through an objective measure of physical activity at 1 year (average measured from 7 days of accelerometry). The protocol has been written according to the Standard Protocol Items: Recommendations for Interventional Trials guidelines.

## Methods and Analysis

### Study Setting

The FIMOUV study is a collaboration between health professionals of the Territorial Hospital Group of Loire centers in France and physical activity professionals on this territory (Figure 1). Patients will be selected at their follow-up consultation, during which the doctor will give the information leaflet and the consent form. FM patients will then be summoned at the University Hospital of Saint-Etienne (Loire) for the inclusion visit (V1). Inclusion and exclusion criteria are detailed in Table 1. We want to compare a supervised training program to physical activity advice, both benefiting from four therapeutic education sessions. Patients are then followed for 1 year (Figure 2).

**Figure 1 F1:**
[figure not shown]
Project collaborators mapping. THGL: Territorial Hospital Group of Loire.

**Table 1 T1:** Eligibility criteria.

Inclusion criteria	Patient over 18 years old
	FM syndrome according to ACR criteria (total score WPI + SSS ≥ 12)
	Language skills in oral and written French
	Sedentary or low level of activity (<150 min of regular physical activity per week at the time of inclusion)
	Affiliation to a social security scheme
	Signing informed consent
Exclusion criteria	Cardiac or respiratory diseases that contraindicate the practice of physical activity
	Severe comorbidities contraindicating the practice of physical activity (rhythm disorders, severe obstructive respiratory failure, gonarthrosis, etc.)
	Impossibility of submitting to medical monitoring of the program for geographical, social, or psychological reasons
	Patient deprived of liberty or patient under guardianship

*FM, fibromyalgia; ACR, American College of Rheumatology; WPI, Widespread Pain Index; SSS, symptom severity scale*.

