### Assessment Measures

The primary outcome of interest will be the long-term therapeutic adherence of FM patients evaluated from an objective measure of physical activity (mean measured from 7 days of accelerometry; Actigraph GT3x, Pensacola, Florida, USA) 1 year after the setup of the organization of care offering initiation and support of APA during 3 months. This sustainability will result in a level of physical activity ≥7.5 MET-h/week at 1 year, corresponding to 150 min of moderate intensity physical activity per week, which is consistent with WHO recommendations.

The secondary objectives will evaluate the impact on the lifestyle (average time of physical activity and sedentary behavior, measured by accelerometry during 7 days), health status, fatigue, sleep, psychic distress, muscular strength and endurance, physical capacity, tolerance to pain and fatigue during training sessions, membership to physical activity, evaluation of the differential cost-effectiveness ratio, and finally an estimate of the budgetary impact of this care strategy.

Details and timetable are shown in Table 2.

**Table 2 T2:** Assessment measures timetable.

	**Inclusion visit V1**	**Intervention 1st month**	**Post-intervention visit V2**	**Intervention 2nd and 3rd months**	**Post-intervention visit V3**	**Intermediate visit V4**	**Final visit V5**

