### Sample Size

Population size is calculated on an expected difference of 20% of the level of MVPA (≥3 METs for metabolic equivalent tasks). Estimating that at baseline, patients are at 3.9 MET-h/week with a standard deviation between 2 and 4 (40), for an alpha risk of 5% and a potency set at 90%, we need to include 150 patients per group; adding an expected dropout rate of 10%, it is necessary to include 165 patients per group to meet the main goal, which means a total of 330 patients.

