### Randomization and Data Collection

Randomization and data collection will be centralized *via* the EnnoV Clinical platform (electronical randomization, Paris, France) and filled in by the referral doctor and the nurse/APA teacher duo. Only investigators and technicians of the study have access to these data.

Patients will be randomized after a multidisciplinary consulting meeting carried out in the presence of the investigators of the study, the referring doctor and, if necessary, with their general practitioner, before the program starts. This meeting aims to decide about the optimal care for the patient. It will be decided if the patient can follow an exercise training. In case of contraindication, the patient will not be randomized into the study.

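### The activity limit for entry is not tied to the accelerometer level that defines sustained adherence, so some patients may already meet that level at V1 and count as adherent without any change

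*Protocol article*

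**What the plan says.** Entry: the eligibility table (Table 1, under Study Setting) requires "Sedentary or low level of activity (<150 min of regular physical activity per week at the time of inclusion". It gives no instrument, intensity or MET value.

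Outcome: the Assessment Measures section opens with "The primary outcome of interest will be the long-term therapeutic adherence of FM patients evaluated from an objective measure of physical activity". The instrument named there is an accelerometer worn for 7 days. The paragraph then sets the level: "This sustainability will result in a level of physical activity ≥7.5 MET-h/week at 1 year". It explains this figure as one "corresponding to 150 min of moderate intensity physical activity per week, which is consistent with WHO recommendations". The level is absolute and does not refer to the patient's own starting value.

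Baseline: the Sample Size section plans as follows: "Estimating that at baseline, patients are at 3.9 MET-h/week with a standard deviation between 2 and 4 (40".

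Timing: Table 2 ticks accelerometry at V1 and at V2 to V5, and places the multidisciplinary meeting and randomisation in the V1 column. The Randomization and Data Collection section says "Patients will be randomized after a multidisciplinary consulting meeting carried out in the presence of the investigators of the study". The only reason it gives for not randomising a patient at that point is a contraindication to exercise training.

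**The concern.** The protocol equates 7.5 MET-h/week with 150 minutes of moderate activity, so the entry limit and the success level are nominally the same line. Nothing in the text ties them to the same measure. Entry counts minutes of regular activity by an unstated method. Success counts MET-hours on a 7-day recording. No printed rule compares the V1 recording with 7.5, and no rule requires a change from V1.

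A patient can therefore satisfy Table 1, be at or above 7.5 on the V1 recording, stay there, and be counted at 1 year as a case of sustained adherence. What is at stake is the meaning of that proportion. The Discussion presents the care organisation's efficacy as illustrated by sustained adherence, so readers will take the proportion as behaviour that the pathway brought about.

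**Working it through.** **1. The protocol's own equivalence.** 150 min = 2.5 h, and 2.5 h × 3 MET = 7.5 MET-h/week. This reproduces exactly, at the 3-MET lower bound that the Sample Size section uses for MVPA.

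**2. Do the two lines coincide on one instrument?** Minutes needed to reach 7.5 MET-h = 7.5 / MET × 60:
- 3 MET: 150 min
- 4 MET: 112.5 min
- 5 MET: 90 min
- 6 MET: 75 min

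At any intensity above 3 MET, fewer than 150 minutes reach 7.5 MET-h. Meeting the entry limit therefore does not guarantee a level below 7.5, even before any difference between instruments.

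**3. Expected share at or above 7.5 at V1.** Inputs are the mean of 3.9, the SD of 2 to 4 and the total of 330 from the Sample Size section. The shape of the distribution is not given, so it is an assumption.

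Normal: P = 1 − Φ((7.5 − 3.9)/SD).

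Log-normal: σ² = ln(1 + (SD/3.9)²), μ = ln 3.9 − σ²/2, P = 1 − Φ((ln 7.5 − μ)/σ). For SD 2, σ = 0.483, μ = 1.244 and z = 1.595. For SD 4, σ = 0.848, μ = 1.002 and z = 1.195.

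| SD | Normal | Log-normal | Gamma |
|---|---|---|---|
| 2 | 3.6% (12 of 330) | 5.5% (18) | 5.6% (18) |
| 3 | 11.5% (38) | 9.7% (32) | 11.5% (38) |
| 4 | 18.4% (61) | 11.6% (38) | 14.9% (49) |

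The normal shape at SD 4 is implausible: it puts Φ(−3.9/4) = Φ(−0.975) = 16.5% of patients below zero MET-h/week. The working range is therefore taken from normal at SD 2 to log-normal at SD 4, that is 3.6% to 11.6%, or about 12 to 38 of 330.

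**4. At the SD implied by the sample size.** A 20% difference is 0.20 × 3.9 = 0.78. Two-sided 5% alpha (assumed two-sided), 90% power and 150 per group imply SD = 0.78 × √(150/2) / (1.960 + 1.282) = 2.08. At that SD the share is 4.2% (normal) to 6.1% (gamma), about 14 to 20 of 330. The issue is smaller there but does not vanish.

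**5. How much of 1-year adherence could be pre-existing?** This depends on how closely a patient's level at 1 year follows the level at V1, which the protocol does not give. As a sensitivity check, assume log-normal levels at both times, a 20% multiplicative gain in the test arm and a correlation of 0.3 to 0.9 on the log scale. Patients already at or above 7.5 at V1 then make up between 13% (SD 2, correlation 0.3) and 59% (SD 4, correlation 0.9) of the test-arm patients at or above 7.5 at 1 year.

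**6. Does their presence shrink the contrast?** In the same check, assuming no gain in the control arm, the difference in proportions is as follows:
- SD 2: 5.63 points in all patients; 5.32 (correlation 0.3) to 4.65 (correlation 0.9) among patients below 7.5 at V1.
- SD 4: 4.75 points in all patients; 4.40 to 3.72 among patients below 7.5 at V1.

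Restricting to patients below the line does not enlarge the difference.

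**The case against.** Much of the case on the other side stands.

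- **Ascertainment is unstated.** A reader might infer that entry rests on what patients declare. The article does not say so. V1 includes both an activity questionnaire and accelerometry, and screening on the recording is neither stated nor excluded. The full protocol may settle it. What remains is that the printed criterion and the printed outcome are not linked.
- **Not all movement counts.** A reader might suppose that any walking or housework pushes patients over 7.5. The Sample Size section defines the level as activity of at least 3 METs, so light activity would not count. The point rests on steps 2 and 3 instead.
- **The endpoint is mostly treated as continuous.** The abstract, the primary objective and the sample size use a mean level. There a high V1 value adds variance and is not a false success. The point applies only to the 7.5 reading, but Assessment Measures puts that reading inside the primary outcome.
- **Randomisation balances these patients.** Bias between arms is not supported. Nor is it shown that the contrast is diluted (step 6).
- **The baseline figures come from a cited study.** If that sample was not selected for low activity, the entry criterion would lower the share.
- **Perfect tracking is not a given.** A reader might divide the V1 share by the 1-year share and call the quotient adherence without change. That requires every patient above the line at V1 to stay above it for a year. Step 5 shows how widely the answer varies when this is relaxed.

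**Conclusion.** The point holds in a limited form. The entry criterion is not tied to the accelerometer level that defines sustained adherence. On the protocol's own baseline figures roughly 4% to 12% of patients, about 12 to 38 of 330, may already meet that level at V1; a normal shape at SD 4 would give 18% but is implausible. Those who stay there count as adherent without any change.

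The range assumes that the planning mean and SD describe the enrolled patients on the same accelerometer measure, and it depends on the assumed shape.

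The comparison between randomised arms remains valid, and the continuous level is not affected in this way. What fails is the interpretation: the proportion at or above 7.5 within an arm mixes activity already present at V1 with activity taken up during the trial, so it cannot be read as adherence produced by the care pathway.

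**What to change.** 1. State in Table 1 how the 150 minutes are ascertained and at what intensity.
2. Keep all randomised patients in the main analysis and adjust the 1-year comparison for the V1 accelerometer level. The tests named under Statistical Analysis are all unadjusted.
3. Alongside it, report in both arms the proportion newly reaching 7.5 MET-h/week among patients below it on the V1 recording. V1 precedes the intervention, so this subset is defined in the same way in both arms.

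The cost is wording plus one more analysis on a slightly smaller subset (about 4% to 12% fewer patients). The V1 recording is already scheduled for every patient.

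Confirming a level below 7.5 on the V1 recording before randomisation is optional. It would cost screen failures of about the same share. It could also delay randomisation, because a 7-day recording would have to be completed and read before the multidisciplinary meeting.

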**Figure 2 F2:**
[figure not shown]
Study design of FIMOUV. THGL, Territorial Hospital Group of Loire.

### Interventions

#### Training Program

##### Test Group

During the first month, the test group benefiting from two weekly exercise sessions of 90 min was supervised by an APA teacher during four consecutive weeks at the hospital. We propose a mixed training program (details on Figure 3), normalized and personalized to each patient profile, as follows:

– Endurance training (Figure 3A): progressive work toward an interval training at an intensity determined during a preliminary cardiorespiratory test (first and second ventilatory threshold, VT1/VT2) and monitored with a heart rate belt connected by Bluetooth (Polar H7, Polar®, Kempele, Finland). A continuous training at VT1 can be proposed if the subject's physical capacity does not allow an increase in workloads as they are made on interval training.– Strength training: whole body circuit training with body weight or small equipment, with at least one exercise soliciting balance, coordination, and/or velocity. Additional loads representing a maximum 50% of one repetition maximum can be added in case of pain evaluation lower than 4/10 on the Borg modified visual analog scale (VAS) at the start of the session. Modalities of training are detailed in Figure 3B.– Stretching and relaxation training (Figure 3C): according to the patient's profile, alternation between passive stretching, cardiac coherence for patients with a high levels of anxiety (measured during V1 thanks to the Hospital Anxiety and Depression scale, HADS), and autogenic training initiation if the fatigue evaluation is higher than 7/10 at the start of the session.

**Figure 3 F3:**
[figure not shown]
FIMOUV program intervention. **(A)** Modalities of aerobic training during the first month of intervention. Each session starts with 10 min warmup and ends with 10 min cooldown. *A continuous training at VT1 can be proposed if the subject's physical capacity does not allow the increase in workloads, as they are made on interval training. (a;b) corresponds to each session of the week; VT1: ventilatory threshold 1; VT2: ventilatory threshold 2. **(B)** Modalities of strength training during the first month of intervention. *Load maximum 50% of 1-repetition maximum if pain evaluation <4/10 at the start of the session. RPE: rating of perceived exertion, Borg modified scale. **(C)** Modalities of relaxation and flexibility training during the first month of intervention. *Hospital Anxiety and Depression Scale >8 for anxiety item. ^$^Fatigue evaluation >7/10 at the start of the session. RHR: resting heart rate. (D) Modalities of therapeutic education program during the first month of intervention.

From the second to third months, each patient is addressed to a relay structure affiliated to the “Sport-Health Houses” of their department to continue a training program for one to two sessions of 60–90 min weekly. Certified by the Ministry of Sports, these health-sport platforms aim to facilitate the maintenance of physical activities among people experiencing health difficulties, with an individualized follow-up. Additionally, a training follow-up booklet will be delivered to ensure the continuity and attendance of training sessions (supervised and autonomous) and evaluate their efficacy on pain and fatigue symptoms thanks to the VAS.

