##### Control Group

The control group receives advice and recommendations for independent physical activity practice at home in order to reach 30 min of moderate intensity physical activity, 5 days a week, as recommended by the World Health Organization (WHO) (current clinical practice).

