**EXERCISE SESSIONS**							
Pain and fatigue tolerance (VAS)		✓		✓			
PA adhesion			✓		✓	✓	✓

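### The test-arm booklet is given the job of showing efficacy on pain and fatigue, but uncontrolled session VAS scores can only describe tolerance and adherence (minor; wording fix)

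*Protocol article*

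**What the plan says.** All references are to the protocol article.

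- **Booklet (Interventions, Test Group, months 2-3 paragraph).** It serves to "ensure the continuity and attendance of training sessions (supervised and autonomous") and also to "evaluate their efficacy on pain and fatigue symptoms thanks to the VAS". The word *their* refers to the training sessions.
- **Month 1 (Test Group).** The test arm has "two weekly exercise sessions of 90 min was supervised by an APA teacher during four consecutive weeks at the hospital".
- **Months 2-3 (Test Group).** Patients go to a community relay structure "to continue a training program for one to two sessions of 60–90 min weekly".
- **Controls (Control Group).** "The control group receives advice and recommendations for independent physical activity practice at home". No training sessions and no booklet are described for them.
- **Objective (Assessment Measures).** The secondary objective that matches the session scores is "tolerance to pain and fatigue during training sessions".
- **Table 2, exercise sessions.** The row is labelled "Pain and fatigue tolerance (VAS") and is ticked for month 1 and for months 2-3, not at any visit.
- **Table 2, screening block.** Separate rows for pain VAS and fatigue VAS are ticked at V1, V2, V3, V4 and V5, with no restriction to one arm.

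**The concern.** Read as written, the booklet sentence gives session scores an evaluative purpose: to show that training works on pain and fatigue, two core symptoms of fibromyalgia. The scores cannot carry that claim, for two reasons.

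First, they lie outside the randomised comparison. With no series in the control arm, a fall over time may reflect natural course or regression to the mean as well as training.

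Second, they are conditional on a session being done and logged. If patients skip or do not log sessions on bad days, the recorded scores over-represent good days.

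A further complication is that start-of-session pain and fatigue scores help decide what the session contains (Test Group section), so score and treatment are not independent.

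What is at stake is a before-after improvement from the booklet being reported as efficacy when the trial holds a better, randomised source for the same symptoms.

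**Working it through.** **1. The passages side by side**

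| Feature | Booklet / session VAS | Visit VAS |
|---|---|---|
| Arms | Test arm only, as described | Not restricted to one arm |
| When a score exists | Only if a session is done and recorded | At each scheduled visit |
| Time covered | Table 2: month 1 and months 2-3 | V1 to V5, up to the final visit |
| Purpose named | Booklet sentence: efficacy. Objective and Table 2: tolerance | No purpose stated beside the rows |

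The session scores thus have two purposes in the article, and only the tolerance purpose fits how they are collected.

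**2. Expected records per test-arm patient**

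- Month 1: 2 per week x 4 weeks = 8.
- Months 2-3: 1 to 2 per week x about 8 weeks = 8 to 16, plus any autonomous sessions.
- Control arm: none described.

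**3. How large a spurious change could be**

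The documents give no pain mean, SD, attendance rate or link between symptoms and recording, so the plan has no figure to reproduce. Everything below is assumed: true pain constant at mean 6/10, between-patient SD 1.5, within-patient SD 1.5, 90% of 8 month-1 sessions recorded, and 70% of 12 later sessions recorded. The log-odds of recording fall by s per pain point in the later period.

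To first order, selection shifts the mean recorded score by

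shift = -s x (1 - p) x variance,

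where p is the recording rate. The within-patient variance (1.5² = 2.25) applies when each patient is compared with himself or herself. The total variance (2.25 + 2.25 = 4.5) applies when all records are pooled.

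| Scenario | Formula | Simulated |
|---|---|---|
| s = 0 | 0 | 0.00 |
| Within patient, s = 0.2 | 0.2 x 0.3 x 2.25 = 0.135 | 0.13 |
| Within patient, s = 0.4 | 0.4 x 0.3 x 2.25 = 0.27 | 0.23 to 0.25 |
| Within patient, same s in both periods, 0.2 | 0.2 x (0.3 - 0.1) x 2.25 = 0.09 | 0.08 to 0.09 |
| Within patient, same s in both periods, 0.4 | 0.4 x (0.3 - 0.1) x 2.25 = 0.18 | 0.16 to 0.17 |
| Pooled records, s = 0.2 | 0.2 x 0.3 x 4.5 = 0.27 | 0.25 to 0.26 |
| Pooled records, s = 0.4 | 0.4 x 0.3 x 4.5 = 0.54 | 0.45 to 0.47 |

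All entries are falls in points. The simulated ranges are with and without truncation of scores to 0-10. The formula overstates slightly at s = 0.4 because it is linear.

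**4. Would such a fall be noticed as an effect?**

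Recorded sessions per patient are 0.9 x 8 = 7.2 and 0.7 x 12 = 8.4. The SD of the within-patient change is about sqrt(2.25/7.2 + 2.25/8.4) = 0.76. With 165 test-arm patients, the standard error is 0.76/sqrt(165) = 0.059. A fall of 0.13 gives z of about 2.2 and a fall of 0.25 about 4.2. With the same dependence in both periods, 0.09 gives about 1.5 and 0.17 about 2.9. A paired before-after test at 5% could therefore be significant with no true effect, although the fall is small on a 10-point scale.

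**The case against.** The strongest case on the other side is that this is one loose word in a description of the intervention. The sentence defines no endpoint, trend or test. Where the article lists objectives and measures, session VAS is already called tolerance. The visit VAS is already scheduled five times, and the Statistical Analysis section gives group comparisons and an intent-to-treat analysis. A condensed article can leave booklet handling to the full protocol or SAP.

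Most of this stands, and it limits the point to a minor one. What remains is that the sentence does state a purpose, the purpose conflicts with the tolerance label, and the data cannot serve it.

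A reader might infer more, and three stronger readings are not supported:

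- **That the trial's evidence on pain and fatigue rests on the booklet.** It does not have to, because the visit VAS allows a randomised comparison that does not depend on session attendance.
- **That the booklet series itself changes setting after month 1.** The booklet is introduced in the months 2-3 paragraph, and nothing says that it covers the hospital month. Only the Table 2 session row spans both periods, and that row is labelled tolerance. The booklet also logs autonomous sessions, so a missed supervised session need not leave a gap.
- **That recorded pain would fall by 0.3 to 0.5 points.** That size comes from pooling records under assumed pain-dependent recording that begins only after month 1. Pooling counts between-patient selection, which a within-patient comparison removes.

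**Conclusion.** The point holds as a minor one. The booklet sentence promises an efficacy evaluation that uncontrolled, recording-dependent session scores cannot deliver, and it disagrees with the tolerance purpose stated in Assessment Measures and Table 2. The lack of a control series is enough to establish this, whatever patients' recording habits are.

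The size of any bias is unknown from the documents. Under the assumptions shown, selective recording alone produces roughly 0.1 to 0.25 points within patients on a 0-10 scale, and nothing if recording is unrelated to symptoms. Natural course and regression to the mean would come on top and cannot be sized here. The accelerometry primary endpoint, the sample size and the visit-based symptom scores are untouched.

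**What to change.** 1. Reword the booklet sentence in the Test Group section so that booklet and session VAS describe tolerance and adherence in the test arm only, with no efficacy claim. This brings it into line with Assessment Measures and Table 2.
2. State that the effect on pain and fatigue is taken from the visit VAS at V1 to V5, compared between randomised groups with adjustment for the V1 value (for example, ANCOVA) in place of the unadjusted t or rank tests named in the Statistical Analysis section.

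The cost is a change of protocol or SAP wording; no new data are needed, because the visit scores are already scheduled. The downside is that session scores can no longer support a statement about efficacy.
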